### Data management and quality control

All enrolled patients will be measured on the scale by professional researchers on the day of enrollment. The researchers are postgraduate students of psychiatry related majors in universities and psychologists in tertiary hospitals. All researchers will receive systematic training in scale measurement to ensure the standardization of scale measurement and data collection:

The clinical scales used in this trial have been widely used nationally and internationally and have good reliability and validity.The researcher will explain the scales and questionnaires using a uniform guideline, and patients will complete the questionnaires and scales under the guidance of the researcher after fully understanding the individual entries.This trial will ensure that all patients will be administered the questionnaire in a quiet indoor environment and the questionnaire will be collected on the spot upon completion to improve data integrity.Questionnaires that meet the following eligibility criteria will be included as valid questionnaires: The age input for the questionnaire is consistent with the age range of the adolescents; The questionnaire is complete with no blanks; The questionnaire is answered carefully and there are no obvious contradictions or patterns in the answers (no more than 10 consecutive questions in one or more scales with the same answer selected).The same brand and model of the therapeutic instrument will be used for treatment to standardize measurement standards and control errors.Statistical data will be entered and checked for accuracy by two persons, and all retrieved data information will be coded, kept, and organized by a specialist.

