**Methods:**

In this pilot randomized controlled trial, 60 participants will be randomly assigned to receive acupuncture or sham acupuncture for 8 weeks of treatment and 4 weeks of follow-up. The primary outcome will be the difference in Children’s Depression Rating Scale-revised (CDRS-R) scores at weeks 0 and 8 of treatment. Secondary outcomes will include 17-item Hamilton Depression Scale (HAMD-17) clinical score reduction rate and clinical remission rate, difference in CDRS-R scores, HAMD-17 scores, 14-item Hamilton Depression Scale (HAMD-14) scores, Pittsburgh Sleep Quality Index scale (PSQI) scores, and Columbia-Suicide Severity Rating Scale (C-SSRS) scores. All outcomes will be assessed at weeks 0, 2, 4, 6, 8 of treatment and week 12 of the follow-up period. In addition, we will assess the safety outcomes from baseline to the end of this trial and feasibility outcome after treatment.

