### Inclusion criteria

Participants who meet the following inclusion criteria will be included: (1) 12 years ≤ age <18 years; (2) Meet DSM-5 diagnostic criteria for “depressive disorders”; (3) Meet mild to moderate ADD (8≤HAMD-17 score < 20); (4) No suicide risk, “No” to all items on the C-SSRS, and a score <3 on item 3 (suicide) of the HAMD-17; (5) No medication (escitalopram, mirtazapine, etc.) or physiotherapy (transcranial magnetic stimulation, transcranial electrical stimulation, acupuncture, electroconvulsive therapy, etc.) received within the past 1 month; (6) Refuse to take the medication; (7) Good reading and writing ability, and able to communicate normally; (8) Volunteer to participate in this study and sign an informed consent form.

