### Secondary outcomes

①HAMD-17 clinical score reduction rate: Pre-treatment HAMD-17 score-HAMD-17 score after 8 weeks of treatment/Pre-treatment HAMD-17 scores.

②HAMD-17clinical remission rate: proportion of HAMD-17 scores <7 after 8 weeks of treatment.

③Difference in CDRS-R scores at weeks 0, 2, 4, 6, 8, 12.

④Difference in HAMD-17, HAMD-14, PSQI, and C-SSRS scores at weeks 0, 2, 4, 6, 8, 12.

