### Statistical analysis

The primary and secondary outcomes of this study will be analyzed using the modified intention to score principle. The other statistical analyses including feasibility outcomes and security outcomes. And the safety analysis will include all patients who have received at least one time of intervention.

Analyses of the primary outcomes will be conducted using linear mixed-effects models (MMRM) and generalized linear mixed models (GLMM) in repeated-measures design, which incorporate the clinical effect rates at weeks 0, 2, 4, 6, 8, and the follow-up period as response variables, as well as baseline values, time with treatment factors, time, and treatment factors as fixed-effects variables for the analyses. This study will assume that missing indicators are randomized, and due to the ability of the MMRM to cope with randomly missing data, this study will not conduct data filling for the primary outcome.

Reliability of our data will be analyzed using Cronbach’s Alpha, which is a commonly used indicator for assessing the internal consistency of a scale (25), and data assessed through the scale are considered reliable only when it is >0.7.

Three sensitivity analyses will be conducted in this study for the primary outcomes. First, the study will exclude missing data and analyzes the complete case dataset. Second, a multiple filling method will be used to fill in the outcomes before conducting the evaluation. Third, the primary outcome will be analyzed based on the set of compliant scenarios. In addition, the study will also conduct subgroup analyses of the primary outcome, which will include gender, age, hospital district, BMI, duration of disease, comorbidities, and medication use. For the analysis of secondary outcome, repeated measures information will also be based on the MMRM method; for other quantitative data outcomes, this study will use the Mann-Whitney U test or t-test, depending on whether the data are normally distributed or not.

Statistical descriptions will be carried out for the adverse reaction indicators, and the method of chi-square test or Fisher’s exact probability will be used to compare the differences between groups.

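### The limit of 10 identical consecutive answers selectively voids forms from participants with few or no remaining symptoms, and can attenuate a true treatment difference

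*Protocol article*

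**What the plan says.** The protocol article, under Data management and quality control, sets a test for which data count: "Questionnaires that meet the following eligibility criteria will be included as valid questionnaires". The conditions concern plausible age, absence of blanks, and careful answering. The last is given a numerical limit: "no more than 10 consecutive questions in one or more scales with the same answer selected". The same section says that "patients will complete the questionnaires and scales under the guidance of the researcher", so the test reaches the rating scales. No scale, visit or type of answer is exempted.

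Three other sections bear on the point:

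- Secondary outcomes defines HAMD-17 remission as the "proportion of HAMD-17 scores <7 after 8 weeks of treatment".
- Statistical analysis states: "This study will assume that missing indicators are randomized". It plans no imputation in the main analysis of the primary outcome. Its sensitivity analyses use complete cases, multiple imputation and a compliant set.
- Sample size says that the results will help to size later trials.

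**The concern.** A cap on identical answers is meant to catch careless responding. On a symptom scale it also catches recovery, because a participant with no symptoms gives the lowest answer to item after item. A HAMD-17 total of 0 is 17 identical answers and fails the rule however carefully it was completed; a total of 0 on the 14-item Hamilton scale fails too. The fewer the remaining symptoms, the likelier the form is to be lost.

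If one arm does better, more of its best results are removed. The observed difference is then too small, and the planned missing-data approach does not correct this. In a pilot, the understated difference would pass into the planning of the next trial.

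**Working it through.** The plan gives no figure for how many forms the rule would void, so there is nothing of its own to reproduce.

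**Inputs from the protocol article.** A run of 11 or more identical answers fails. The HAMD-17 has 17 items and the other Hamilton scale has 14. Remission is a HAMD-17 total of 0 to 6.

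**Assumed, not in the document.** The lowest answer is coded 0; non-zero items fall at random positions; remission rates, means, SD and points per non-zero item are as stated below.

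**Step 1: which forms fail within one scale.** Take n items, k of them non-zero. The non-zero items leave k + 1 gaps for the zeros. Two runs of 11 would need 22 items, so at most one fits in 17 or 14. The number of failing arrangements is therefore (k + 1) × C(n − 11, k), out of C(n, k). For n = 17 and k = 2: 3 × C(6, 2) = 3 × 15 = 45, out of C(17, 2) = 136.

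| Non-zero items | HAMD-17, failing / all | Share voided | 14-item scale, failing / all | Share voided |
|---|---|---|---|---|
| 0 | 1/1 | 100% | 1/1 | 100% |
| 1 | 12/17 | 70.6% | 6/14 | 42.9% |
| 2 | 45/136 | 33.1% | 9/91 | 9.9% |
| 3 | 80/680 | 11.8% | 4/364 | 1.1% |
| 4 | 75/2380 | 3.2% | 0/1001 | 0 |
| 5 | 36/6188 | 0.6% | 0/2002 | 0 |
| 6 | 7/12376 | 0.06% | 0/3003 | 0 |
| 7 or more | none | 0 | none | 0 |

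**Step 2: if runs are counted across scales.** The wording leaves this open. With the 17- and 14-item scales treated as one sequence of 31 items, a simulation gives about 99% voided with 2 non-zero items, 73% with 4, 38% with 6 and 14% with 8. The ambiguity changes the size of the problem considerably.

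**Step 3: remission rates.** Let p be the true rate and f the share of remitters' forms voided, with no other forms lost. The observed rate is p(1 − f)/(1 − pf). For assumed true rates of 40% and 20%:

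| f | Observed rates | Difference (true: 20.0 points) |
|---|---|---|
| 10% | 37.5% vs 18.4% | 19.1 |
| 25% | 33.3% vs 15.8% | 17.5 |
| 50% | 25.0% vs 11.1% | 13.9 |

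With true rates of 30% in both arms, the observed rates fall together (24.3% in each at f = 25%) and the difference stays 0.

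**Step 4: HAMD-17 means at week 8.** A simulation used an assumed SD of 4.5, about 1.4 points per non-zero item, and the within-scale probabilities from Step 1.

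| Target means | Remitters' forms voided | True difference | Difference in retained forms |
|---|---|---|---|
| 7 vs 10 | about 30% vs 19% | −2.90 | −2.32 |
| 5 vs 9 | about 39% vs 22% | −3.75 | −2.77 |
| 10 vs 10 | about 19% in each | 0 | 0 |

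The retained difference is 2.32/2.90 = 80% of the true one in the first case and 2.77/3.75 = 74% in the second. These figures use week-8 forms alone. A mixed model that also uses earlier valid visits would recover part of the loss.

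**Step 5: the missing-data assumption.** Missing at random requires that, given the data retained, missingness does not depend on the value lost. Here the form is lost because of its own answers. Complete-case analysis keeps the loss, multiple imputation normally rests on the same assumption, and the compliant set does not bring voided forms back.

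**The case against.** The strongest reply concerns scope. The only timing in that section is the day of enrolment, when HAMD-17 must be at least 8 and nobody is in remission. The cap stands in parentheses as an illustration of careful answering, and the article does not say how an invalid form enters the model. This is fair as to certainty. But nothing confines the rule to baseline, the sentence names scales, and an unqualified validity criterion will be applied as written when the data are cleaned.

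Several stronger readings are tempting, and the document does not support them.

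- *Remitted participants are discarded.* The rule voids forms, not people, and earlier valid visits stay in the model. Whole participants would be lost only if the dropout criterion on incomplete or inaccurate information, or the removal criterion on compliance, were applied to such forms; the article does not say so. Remission also extends to a total of 6, and six items scoring 1 each are voided only 0.06% of the time within the scale.
- *Half of remitters are lost.* The 50% row is an illustration only. The simulations gave about 19% to 39%, themselves on assumed values.
- *The primary result shrinks by a known amount.* The article gives no CDRS-R item count, so no size can be attached to that outcome.
- *The entry rule breaches the cap.* Eligibility requires a negative answer "to all items on the C-SSRS, and a score <3 on item 3 (suicide) of the HAMD-17". That is a uniform pattern, but the C-SSRS item count is not given, so a breach cannot be shown.
- *The blank rule has the same bias.* "The questionnaire is complete with no blanks" is a separate condition with no shown link to remission.

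The objection also rightly notes that the rule creates no false difference when the arms are equal.

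**Conclusion.** The concern holds in a limited form. Followed as written, the cap removes every all-zero HAMD-17 or 14-item form and, on random item positions, about 71%, 33% and 12% of HAMD-17 forms with one, two or three non-zero items. Within one scale the risk is slight from four non-zero items on; it is much greater if runs are counted across scales. The loss depends on outcome and contradicts the missing-at-random assumption.

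Where the arms truly differ, the HAMD-17 difference and the remission rates can be pulled towards no effect, by roughly a fifth to a quarter of the mean difference in the simulated week-8 cases and by less once earlier visits contribute. The enumeration is exact under its one assumption about item position. The sizes of attenuation rest on assumed rates, means and spread, and are illustrations.

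**What to change.** In Data management and quality control, change the identical-answer limit from a validity criterion to a query trigger. A run of more than 10 identical answers prompts the assessor to confirm the answers with the participant while still present, and the confirmation is recorded. Keep all completed outcome scales in the main analysis and exclude flagged forms only in a sensitivity analysis. State whether runs are counted within a scale or across scales.

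The cost is wording only, since forms are already collected on the spot. The check need not be deleted, and no proration rule is needed to answer this point. The small downside is that some carelessly answered forms may stay in the main analysis; the sensitivity analysis shows whether they matter.

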## Ethics and dissemination

Participants under the age of 18 will be enrolled in this trial, and written consent must be provided by a guardian in addition to the participant’s own informed consent (see *Appendix2.* for details). The trial protocol has been approved by the Ethics Committee of the Affiliated Traditional Chinese Medicine Hospital, Guangzhou Medical University (approval number 2024NK73). The principle of informed consent is strictly enforced in research, and informed consent documents will be used to explain to participants in concise terms the dedication and benefits of participating in research and how their rights and interests will be protected prior to their participation in the trial. The researchers will be responsible for checking that informed consent has been obtained from each participant or their legal representative and that the informed consent document is properly signed and dated prior to any step in the trial protocol and prior to administration of the trial medication. This trial will be conducted in compliance with the ethical principles declared in the latest version of the Declaration of Helsinki, the corresponding guidelines of the Code of Clinical Trial Practice, as well as the laws and regulations of China, to provide protection for the participants. The results of this trial will be made publicly available on the registration platform. There will be no use of any professional writers for this trial. Future authorship of trial publications will be based on the authors’ contributions.

## Discussion

Acupuncture has been documented to treat mood disorders since ancient times. Recent studies have shown that acupuncture has the advantages of low cost and fewer side effects compared to pharmacotherapy (26), so acupuncture is considered a promising non-pharmacological treatment to reduce depressive symptoms and can be used as an alternative or complementary treatment to pharmacotherapy to improve outcomes (27). And research on its mechanism of effect is gradually increasing.

It has been suggested that the antidepressant effects of acupuncture can be explained by the regulation of neurotransmitters, gut flora (28), neuroplasticity (29), inflammation (30), and other molecular mechanisms. Results from animal experiments suggest a multitarget antidepressant effect of acupuncture, which may be related to amino acid metabolism and inflammatory pathways (31). In addition, similar to antidepressant medications, acupuncture is capable of affecting the neurotransmitter levels of serotonin and noradrenaline (32). And for adolescents, fluctuations in neurotransmitter systems, such as GABA, NMD, and dopamine have profound impact on neural signaling in regions pertaining to emotion regulation. GABAergic and glutamatergic systems in the PFC and cingulate cortices have a direct impact on the excitability and plasticity in regions subserving emotion regulation (33). Thus, acupuncture may be able to treat ADD by producing fluctuations in the neurotransmitter system to achieve a mood-modulating effect. There’s also the fact that synapses in the adolescent brain are highly dynamic, new synapses are formed and others eliminated at higher rates than seen in adults (34) (35). So, adolescents may be more sensitive to the modulating effects of the neurotransmitter system produced by acupuncture. However, there is a lack of clinical evidence about whether acupuncture can treat adolescent depression at present.

Traditional Chinese medicine (TCM) believes that brain is the house of original spirit, which means that the brain can govern the body’s conscious thought and mental activity, also play a key role in regulating emotional responses (36). Therefore, acupuncture on meridians and points related to the brain can achieve the effect of regulating and awakening the mind as well as regulating emotions. So, we choose acupoints in the head, GV20 and GV29, to achieve the effect of inducing resuscitation and improving mood. “Heart stores spirit”, means that the heart has the function of governing life activities, regulating feelings thinking cognition, and dominating emotional activities (37). HT7, the gateway for the entry and exit of the mind and spirit, can nourish heart and tranquilize the mind. In general, TCM considers the pathogenesis of depression to be stagnation of qi, imbalance of yin, yang, qi and blood in the zang-fu organs (38). Therefore, we choose CV17, PC6, LR3, and SP6 these acupoints to regulate qi and blood, restore the balance of yin and yang in the organism and achieve the effect of improving depression.

There are certain limitations that exist with this trial. Firstly, this trial will only involve a 4-week post-treatment follow-up and will not involve evaluation of long-term outcomes and recurrence. Secondly, this trial will be evaluated using subjective scales, and the participants included are relatively young, which may bias the results due to comprehension error. Thirdly, this trial will be confined to a single-center trial involving 60 patients, potentially introducing selection bias. Nevertheless, for future trials, we aim to recruit patients from multiple centers in a significantly larger sample size to mitigate these limitations
